## Primary Outcome

The primary outcome is the optimal adaptive intervention strategy derived through reinforcement learning algorithms, quantifying personalized temporal allocations for virtual reality Taichi (VRTC), offline Taichi (OffTC), and cognitive training (CT) in clinically implementable 5-minute intervals.

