## Study Endpoints/Events/Outcomes

## Primary Aim

Determine the optimal adaptive intervention strategy for older individuals with MCI using a causality-driven dynamic treatment regime framework.

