## Secondary Outcomes

Average treatment effects (ATE) of cognitive scores measured by Memory Guard.

Individual treatment effects (ITEs) across participant subgroups with different baseline characteristics.

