## Sample Size and Power Analysis

The study size was determined based on response rate parameters drawing from multicomponent intervention studies and previous response rates. We calculated a required sample of 54 participants in the intervention group (assuming 0.60 response rate, 0.05 type I error, 0.45 half-width confidence interval, and 0.80 statistical power).

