### Outcome Assessment

Participants' cognitive function will be monitored using the Memory Guard assessment tool at predetermined intervals (baseline, week 12, and week 24).

[figure not shown]

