## Statistical Considerations

**Average Treatment Effects**

We will use causal forests double machine learning to estimate:

Total ATE between treatment and control groups on cognitive outcomes

Component-specific ATE for VRTC, OffTC, and CT

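### The primary outcome is the strategy the algorithm returns, not a participant outcome with a comparator, so an optimal strategy is obtained from any data

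*Protocol*

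**What the plan says.** The Primary Aim reads "Determine the optimal adaptive intervention strategy for older individuals with MCI using a causality-driven dynamic treatment regime framework". The Primary Outcome section matches it: "The primary outcome is the optimal adaptive intervention strategy derived through reinforcement learning algorithms", expressed as personal time allocations for VR Taichi, offline Taichi and cognitive training. Neither section names a participant measurement, a comparator or a criterion for judging the strategy.

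Memory Guard is administered at baseline, week 12 and week 24 (Outcome Assessment), but as an endpoint it appears only under the Secondary Aim and Secondary Outcomes: "Average treatment effects (ATE) of cognitive scores measured by Memory Guard". Statistical Considerations plans "Total ATE between treatment and control groups on cognitive outcomes", component-specific effects and SHAP values. It does not describe how the derived strategy will be valued or compared.

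Procedures Involved randomises to two first-stage packages plus a control group. Non-responders at week 12 are re-randomised to switch or to a doubled dose, which gives four embedded regimes. No stated aim, outcome or analysis contrasts them. Sample Size and Power Analysis asks for 54 people across the active arms, and the inputs it lists for that figure are "assuming 0.60 response rate, 0.05 type I error, 0.45 half-width confidence interval, and 0.80 statistical power". About 30 participants per arm are planned (Local Number of Participants).

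**The concern.** A primary outcome should be something measured on participants whose value could come out well or badly. A fitted policy is neither. The optimiser selects the action with the highest estimated return, and it does so on pure noise as readily as on a real signal. As written, the trial will report an optimal personalised strategy even if tailoring adds nothing over giving everyone the same package, or over control.

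The second risk is selection. The option that looks best in a small sample looks better than it is, and finer tailoring makes this worse. The section on the added value of the study already presents personalised combinations and individual effects of 0.94 and 1.12 from the trial's own participants. Its average effect of 0.587 (95% CI 0.022 to 1.152) concerns the intervention, not the derived strategy.

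**Working it through.** **The plan's own figure.** Assume 1:1 allocation at both stages and outcome SD 1. Responders consistent with a regime then get weight 2 and re-randomised non-responders weight 4. With response rate r, the variance factor of one weighted regime mean is 4 − 2r, which at r = 0.60 is 2.8. Then N = 1.96² × 2.8 / 0.45² = 3.8415 × 2.8 / 0.2025 = 53.1, rounded up to 54. This matches the stated size, but the route is inferred. A one-sided 5% half-width for the first-stage difference gives 4 × 1.645² / 0.45² = 53.4, also 54. The stated power of 0.80 enters neither formula. Neither route sizes the trial to evaluate a learned strategy.

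**Precision at about 60 intervention participants (30 + 30).**
- One regime mean: 1.96 × √(2.8/60) = 0.42 SD.
- Difference between two regimes with different first-stage arms: 1.96 × √(5.6/60) = 0.60 SD.

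Both are before baseline adjustment.

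**Optimism when nothing differs.** Inputs from the protocol are N ≈ 60 and 60% response. Assumed inputs are SD 1, 1:1 allocation at both stages and no true difference between any options. The true advantage is therefore zero, and anything above zero is selection.

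| Rule, valued on the data that selected it | Apparent advantage (SD) |
|---|---|
| Best of the four embedded regimes, no tailoring | 0.20 |
| Better first-stage arm within 4 cells | 0.21 |
| Better first-stage arm within 8 cells | 0.30 |
| Better first-stage arm within 16 cells | 0.35 |
| Best of four regimes within 4 strata | 0.41 |

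These are simulation results. The 4- and 8-cell rows can be checked by hand. The larger of two independent means of m observations exceeds its expectation by about 0.564/√m, where 0.564 = 1/√π. With m = 7.5 per arm and cell this is 0.21; with m = 3.75 it is 0.29.

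At 16 cells the approximation breaks down. The chance that a given arm of 30 is absent from a cell is (15/16)³⁰ = 0.144, so at least one arm is missing with probability 1 − (1 − 0.144)² = 0.27. That is about 4 of 16 cells, and the 0.35 depends on how those cells are handled. Sixteen cells corresponds to the four state variables named in the protocol (cognitive status, age, diabetes, hypertension) if each is made binary, which is an assumption.

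**Against control.** Under the same null with 30 controls, a naive test of the selected best regime (z > 1.96) rejected in 9.4% of simulated trials, against a nominal 2.5%. Not all of that excess need be due to selection, because the variance estimate had no small-sample correction.

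**The case against.** Four points have force.

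- **The SAP is not at hand.** Cross-fitting or held-out evaluation of a policy is ordinary SAP content. A reader might infer that the benefit will certainly be overstated, but no section says the strategy will be valued on its training data. The inflation is therefore conditional. An SAP could not cure the rest, because the protocol itself fixes the primary outcome and fixes it as algorithm output.
- **A SMART is meant to build strategies.** An estimation aim needs no pass/fail test, so the absence of a hypothesis test is not itself the defect. An estimate still needs a target quantity on participants, and none is named.
- **The randomised data are used.** A reader might infer that the primary question ignores the randomised sequences. That goes too far: the strategy is to be learned from them. What is missing is a stated contrast of the regimes or of the learned strategy. The planned treatment-versus-control effect is secondary and does not evaluate the strategy.
- **The size is scenario-dependent.** The real policy allocates time in small steps across three components, which is not the action space simulated. It is also tempting to say that 0.35 SD is most of the half-width the trial was sized for. The protocol gives 0.45 without a unit, so that comparison is not supported.

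**Conclusion.** The point stands in this form. The primary outcome is a fitted object with no participant measure and no comparator, so the primary aim yields a strategy called optimal whatever the data show. This is read directly from the Primary Aim and Primary Outcome sections and rests on no calculation.

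The size of any overstatement is an illustration: about 0.20 SD without tailoring and 0.21 to 0.35 SD for simple tailoring of the first stage. It depends on same-data evaluation, SD 1, 1:1 allocation, no true differences and a simplified set of actions. It does not show that the effects already reported in the protocol are wrong by these amounts.

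**What to change.** 1. Name the week-24 Memory Guard score as the participant-level outcome on which strategies are judged.
2. Estimate its mean under each of the four embedded regimes by weighted regression, adjusted for the baseline score. Use the actual randomisation probabilities, which the protocol does not state; the relative weights are 2 and 4 if allocation was 1:1 at both stages.
3. Report the learned policy's cross-fitted value with a 95% CI, minus control and minus the best fixed regime. Select that regime within the training folds too; otherwise its own optimism biases the comparison against the policy.
4. Call the policy optimal only if the difference supports it; otherwise label it hypothesis-generating.
5. Label the changed primary outcome and the added analyses as post hoc, because the protocol already reports results.

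No new data are needed. The cost is rewording, extra analysis and wide intervals: about ±0.42 SD for one regime mean and ±0.60 SD for a difference between regimes with different first-stage arms, before baseline adjustment. A headline this imprecise may well not support the word optimal, and the report should be ready to say so.

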### Enabling Dynamic Decision-Making

MCI management requires making sequential treatment decisions over time, particularly as patients' cognitive status changes[33,34]. The SMART design mirrors this clinical reality by incorporating decision points where intervention strategies can be modified based on interim outcomes. This approach allows us to answer critical questions about when to intensify, switch, or maintain interventions based on early response indicators.

Specifically, our design includes an assessment of intervention mastery at week 12, with non-responders being re-randomized to either alternative interventions (switching from offline Taichi to VR Taichi or vice versa) or intensified interventions (doubled doses). This mirrors clinical practice where practitioners typically adjust treatment approaches when patients show insufficient progress.

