## Procedures Involved

This study employs a prospective sequential, multiple assignment, randomized trial design. The 24-week SMART design comprises two 12-week phases. In the first phase, eligible participants will be randomly assigned to receive either offline Taichi plus cognitive training (OffTC+CT) or virtual reality Taichi plus cognitive training (VRTC+CT). Each intervention will consist of 1-hour weekly exercise combined with 1 hour weekly cognitive training.

At week 12, participants will be assessed for intervention mastery, with non-responders (defined as those subjectively unable to master the intervention content, scoring less than 3 on a 5-point Likert scale) being re-randomized to alternative or intensified interventions for the second 12-week phase. Responders in Group OffTC+CT will continue their original intervention protocol, while non-responders will be randomly assigned to either VRTC+CT or doubled doses of their original intervention (2OffTC+2CT). Similarly, responders in Group VRTC+CT will maintain their initial protocol, while non-responders will be randomly assigned to either OffTC+CT or doubled doses of their original intervention (2VRTC+2CT). The control group will receive only health education and routine care throughout the 24-week period.

The anticipated duration for individual participation in the study is 24 weeks (6 months). The duration anticipated to enroll all study participants is approximately 9 months (April to December 2023).

[figure not shown]

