**First-Phase Intervention (Weeks 1-12)**

All participants assigned to intervention groups will receive either:

Offline Taichi plus cognitive training (OffTC+CT): 1-hour weekly OffTC sessions plus 1-hour weekly cognitive training

Virtual reality Taichi plus cognitive training (VRTC+CT): 1-hour weekly VRTC sessions plus 1-hour weekly cognitive training

The control group will receive health education and routine care.

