**Second-Phase Intervention (Weeks 13-24)**

Responders will continue their original intervention protocol. Non-responders will be re-randomized to either:

Alternative intervention: Switching from OffTC+CT to VRTC+CT or vice versa

Intensified intervention: Doubled doses of their original intervention (2OffTC+2CT or 2VRTC+2CT)

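### The primary outcome promises separate 5-minute allocations of three components, but the delivered packages tie cognitive training to Taichi time and contain no mixed or intermediate doses

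*Protocol*

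**What the plan says.** The Primary Outcome section makes the result a strategy obtained by reinforcement learning, "quantifying personalized temporal allocations for virtual reality Taichi (VRTC), offline Taichi (OffTC), and cognitive training (CT) in clinically implementable 5-minute intervals".

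The intervention sections describe something much coarser. Under Procedures Involved, "Each intervention will consist of 1-hour weekly exercise combined with 1 hour weekly cognitive training". Under First-Phase Intervention (Weeks 1-12), one active arm receives "1-hour weekly OffTC sessions plus 1-hour weekly cognitive training" and the other "1-hour weekly VRTC sessions plus 1-hour weekly cognitive training". Under Second-Phase Intervention (Weeks 13-24), "Responders will continue their original intervention protocol", while non-responders (mastery score below 3) are re-randomised to a switch of Taichi form or to the doubled package: "Intensified intervention: Doubled doses of their original intervention (2OffTC+2CT or 2VRTC+2CT"). Control participants receive health education and routine care only.

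No section schedules, randomises or bounds any other dose.

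**The concern.** Randomisation supports a treatment rule only over the choices that were randomised. The primary outcome asks for three separate quantities of time on a fine scale. The design varies one package choice at baseline and, for non-responders only, one further package choice at week 12. The gap between the two has to be filled by the model's functional form.

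The primary result is at stake. The Protocol's Added value and Implications sections present the output as specific guidance for community use. If the minute-level split between cognitive training and Taichi is not identified by the design, that guidance lacks the randomised basis on which the Protocol justifies choosing a SMART over observational work.

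**Working it through.** **1. The Protocol's own sample size.** The inputs, from Sample Size and Power Analysis, are response rate r = 0.60, type I error 0.05, half-width h = 0.45 and power 0.80, with 54 required in the intervention group. Take the mean outcome under one embedded regime, with 1:1 randomisation at both stages. Responders carry weight 2 and non-responders weight 4, so the variance factor is 2r + 4(1 − r) = 2(2 − r) = 2.8. With SD = 1 (assumed) and a two-sided interval:

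N = 2.8 × (1.96 / 0.45)² = 2.8 × 18.97 = 53.1, rounded up to 54.

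The figure reproduces. The 0.80 power plays no part in it; adding a power term would give 108.5. On this reading, 54 is a precision target for one fixed regime and not for a three-component dose surface.

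**2. What is delivered.** Weekly minutes, from Procedures Involved and the two phase descriptions:

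| Package | VRTC | OffTC | CT |
|---|---|---|---|
| Control | 0 | 0 | 0 |
| OffTC+CT | 0 | 60 | 60 |
| VRTC+CT | 60 | 0 | 60 |
| 2OffTC+2CT | 0 | 120 | 120 |
| 2VRTC+2CT | 120 | 0 | 120 |

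The switch option adds no new row, because it moves a participant between the second and third active packages listed above at the single dose.

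**3. Identification.** In every row CT = VRTC + OffTC, so the three dose columns have rank 2. An effect per minute of CT cannot be told apart from an effect per minute of Taichi of either form. Averaging dose over the 24 weeks does not help. The seven treatment paths (control, plus three from each active arm) give six distinct points, because both switch paths average to (30, 30, 60). The same identity holds at all six, so the rank is still 2.

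**4. Size of the gap.** The Protocol gives no bounds for the action space. Assume 0 to 120 minutes, the largest assigned dose. Steps of 5 minutes give 25 levels per component and 25³ = 15,625 allocations.

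- The convex hull of the five packages is the set with VRTC + OffTC ≤ 120 and CT = VRTC + OffTC. On the grid this holds 25 × 26 / 2 = 325 points, and 325 / 15,625 = 2.1%. About 98% therefore lie outside.
- Apart from the five packages themselves, the points inside the hull are interpolation. No weekly package takes those values either.
- The share of allocations actually delivered depends on the bounds chosen:

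| Assumed action space | Delivered / possible | Share |
|---|---|---|
| Each component 0 to 120 | 5 / 15,625 | 0.03% |
| Total time at most 240 | 5 / 13,025 | 0.04% |
| Each component 0 to 60 | 3 / 2,197 | 0.14% |
| One Taichi form, CT free | 5 / 1,225 | 0.41% |
| One Taichi form, CT tied to Taichi | 5 / 49 | 10% |

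Only the last row rises above 0.5%, and it is no longer a three-component allocation.

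**5. Second-stage support.** Local Number of Participants gives about 30 in each active arm, so about 60. With r = 0.60, 60 × 0.40 = 24 participants are re-randomised, and 24 / 4 cells = 6 per cell. (With 54 participants: 21.6 and 5.4.) Each doubled package is seen in about 6 people, all of them non-responders. At this stage nobody is randomised between 60 and 120 minutes of the same Taichi form, because the alternative to doubling is the other form at the single dose.

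**The case against.** The strongest reply is that the Protocol is open about model dependence. It says the strategy is derived by reinforcement learning and nowhere says that 5-minute steps are randomised. An analysis plan, not shown here, may bound the action space or specify the reward and training. That stands as far as it goes. But an analysis plan can only restrict actions; it cannot supply dose levels or a CT contrast that the design never delivers. Variation in attendance would alter the minutes received, but not at random.

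Several stronger readings are tempting and should not be drawn.

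- A reader might take 5 of 15,625 as the measure of the problem. That ratio rests on an assumed upper bound, and any finely gridded dose model has near-zero cell coverage. The tie between CT and Taichi time and the convex hull are the better evidence.
- A reader might call every unassigned allocation extrapolation. Those inside the hull, such as one Taichi form between 0, 60 and 120 minutes with CT matched, are interpolation.
- A reader might infer that the learner will be biased towards untried doses. The Protocol does not describe training or constraints, so no direction of error can be stated.
- A reader might see a contradiction in Enabling Dynamic Decision-Making, which says "This approach allows us to answer critical questions about when to intensify, switch, or maintain interventions based on early response indicators". The next paragraph of that section specifies week-12 re-randomisation of non-responders to an alternative or intensified intervention. Not re-randomising responders is a normal SMART feature, and the embedded regimes remain comparable. This is a matter of wording only.

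**Conclusion.** The point holds and concerns the primary outcome. The delivered packages cannot identify a CT allocation separate from Taichi time, and they give no data on mixed weekly allocations or on doses between 0, 60 and 120 minutes. The rank result follows from the package definitions and needs no assumption beyond reading a doubled dose as twice the weekly minutes. The figure of about 98% outside the hull assumes a 0 to 120 minute grid. The figures of about 24 re-randomised and about 6 per cell assume the Protocol's 0.60 response rate, about 60 active participants and equal re-randomisation. What the design does support is a comparison of first-stage packages, of switch versus intensify among non-responders at week 12, and of the regimes built from these, all with limited precision at the second stage.

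**What to change.** Reconcile the Primary Outcome section with Procedures Involved and the two phase descriptions, without this review taking a view on which doses are right.

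1. Define the primary policy over the randomised actions: the first-stage package, and switch versus intensify for participants with mastery below 3. Include control in the first-stage set only once two sections agree on it. Study Intervention describes random assignment to control or intervention, whereas Procedures Involved describes first-phase randomisation between the two active packages only.
2. Compare the embedded regimes, and report the uncertainty and the number of participants behind each. State that personalising the second-stage choice rests on about 24 people, about 6 per cell. Restricting the action set makes the policy randomised; it does not make it precise.
3. Report any allocation "in clinically implementable 5-minute intervals" as exploratory model output, labelled as not randomised, with the number of participants at or near each recommended allocation. Make no claim of a separately identified CT allocation.
4. As a minor wording change, limit the claim in Enabling Dynamic Decision-Making to switch versus intensify among non-responders at week 12.

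No new data are needed. The policy learner is re-run on a discrete action set and the primary outcome is reworded. The cost is a less granular headline, which matters because computing personalised intensities is a stated purpose of the study. That output stays in the report as exploratory.

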## Secondary Outcomes

Average treatment effects (ATE) of cognitive scores measured by Memory Guard.

Individual treatment effects (ITEs) across participant subgroups with different baseline characteristics.

## Sample Size and Power Analysis

The study size was determined based on response rate parameters drawing from multicomponent intervention studies and previous response rates. We calculated a required sample of 54 participants in the intervention group (assuming 0.60 response rate, 0.05 type I error, 0.45 half-width confidence interval, and 0.80 statistical power).

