### Identifying Optimal Treatment Sequencing

The optimal ordering of multicomponent interventions is a critical but understudied aspect of MCI management. A SMART design can determine whether treatment sequences matter - for instance, whether initiating with VR Taichi followed by offline Taichi for non-responders produces different outcomes compared to the reverse sequence.

This is particularly relevant given recent evidence suggesting potential synergistic effects between different intervention modalities. For example, Boa Sorte Silva et al. (2024) and has demonstrated that combined exercise and cognitive interventions may yield greater benefits than single-component interventions[35].

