## Vulnerable Populations

## Local Number of Participants

92 participants will be enrolled (approximately 30 each for OffTC+CT and VRTC+CT, and approximately 30 for control).

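### The sample-size statement attaches 0.80 power to a figure of 54 that reproduces only as a precision calculation, with no comparison or effect size named for the power

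*Protocol*

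**What the plan says.** The section Sample Size and Power Analysis gives one result: "We calculated a required sample of 54 participants in the intervention group". It lists four inputs: "assuming 0.60 response rate, 0.05 type I error, 0.45 half-width confidence interval, and 0.80 statistical power". The response rate is said to come from earlier multicomponent studies. The section does not say what the interval is for, what unit 0.45 is in, or which hypothesis the power refers to.

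Enrolment is set under Local Number of Participants: "92 participants will be enrolled (approximately 30 each for OffTC+CT and VRTC+CT, and approximately 30 for control". That puts about 60 people in the two intervention arms together, so 54 must be a total over both arms and not a number per arm.

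Under Procedures Involved, intervention participants are randomised between two first-stage treatments. At week 12 only non-responders are re-randomised, to a switch or to a doubled dose, which gives four embedded regimes. Study Intervention gives comparison of adaptive interventions as the purpose of the design. Secondary Outcomes and Statistical Considerations add an average treatment effect against control.

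**The concern.** A half-width is a precision target: it needs a confidence level and a variance, and no power. Power needs a hypothesis and a difference to detect. The sentence lists both kinds of input as if they led jointly to 54, and supplies neither the hypothesis nor the difference.

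This is the trial's only justification of its size. A reader who sees 0.80 will assume that some comparison in the trial has an 80% chance of detecting an effect that matters, and will read a null comparison as informative. If the 0.80 played no part in the calculation, that reading has no basis.

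**Working it through.** **Inputs from the protocol.** Response rate 0.60, so 0.40 are non-responders; type I error 0.05; half-width 0.45; power 0.80; 54 intervention participants; about 30 per arm enrolled.

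**Assumptions.** 0.45 is in SD units with a common SD of 1; two-sided testing; 1:1 randomisation at both stages (the first inferred from about 30 each); no dropout; no covariate adjustment.

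**Step 1: reproduce 54.** For the weighted mean of one embedded regime, responders carry weight 2 and non-responders weight 4, so N × variance = 2(0.60) + 4(0.40) = 2.8. Then

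N = 2.8 × (1.96/0.45)² = 53.1, or 26.6 per first-stage arm. Rounding up to 27 per arm gives 54.

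The half-width at 54 is 1.96 × √(2.8/54) = 0.446. The response rate, the type I error and the half-width are all used; the 0.80 is not.

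**Step 2: look for a reading in which 0.80 does enter.**
- Difference of 0.45 SD between regimes with different first treatments: 2 × 2.8 × ((1.96 + 0.842)/0.45)² = 217. With a power term, 54 corresponds to 0.90 SD.
- 80% assurance that the half-width is at most 0.45: about 64 by simulation. At 54 the assurance is about 65%.
- Ordinary two-sample comparison of means at 0.45 SD: 78 per arm two-sided, 62 one-sided.
- One-sample test of a single regime mean against a fixed value: 2.8 × ((1.96 + 0.842)/0.45)² = 108.5 in total, or 54.3 per first-stage arm. The 54 appears here, but per arm, which conflicts with 54 for the intervention group and about 30 per arm.

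**Step 3: what the design gives at 0.45 SD, unadjusted.**

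| Comparison | Size | Power at 0.45 SD | Detectable at 80% |
|---|---|---|---|
| Regimes, different first treatment | N = 54 | 29% | 0.90 SD |
| Same | N = 60 | 31% | 0.86 SD |
| Regimes, shared first treatment | N = 54 | 46% | 0.68 SD |
| Same | N = 60 | 50% | 0.65 SD |
| OffTC+CT v VRTC+CT | 30 v 30 | 40% | 0.74 SD |
| Intervention v control | 60 v 30 | 51% | 0.63 SD |
| Switch v double, non-responders in one arm | 6 v 6 | 11% | 1.8 SD |

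Formulas:
- Different first treatment: SE = √(5.6/N), which is 0.322 at 54 and 0.306 at 60. Power = Φ(0.45/SE − 1.96); detectable difference = 2.80 × SE. A simulation with estimated variances gave 32% and 35%, close to the formula. One-sided, the 29% becomes 40%.
- Shared first treatment: responders are common to both regimes and cancel, so SE = 0.4 × √(2/k), where k is the number of non-responders per option. At N = 60, k = 30 × 0.4/2 = 6 and SE = 0.231.
- The last three rows are two-sample t calculations.

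The last row is on a different scale from the others. It is an effect among non-responders only, and on the regime scale it is multiplied by 0.4: 1.8 × 0.4 = 0.72 SD. The 0.65 SD for the same contrast is a normal approximation and is somewhat optimistic with 6 per option.

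**The case against.** The strongest objection is that the protocol calls 0.45 a half-width and nowhere a difference to detect. A reader might infer that the trial has 29% power against its own target, or that it should have enrolled about 217 intervention participants. Neither follows, because no target difference is stated. This stands, and the power figures serve only to show what the 0.80 cannot mean.

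Second, the SD unit is an assumption. The protocol gives no scale for 0.45 or for Memory Guard. That 54 reproduces exactly makes the reading likely, but does not prove it.

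Third, a reader might infer that no comparison can reach 80% power at 0.45 SD. That holds only without adjustment. Memory Guard is measured at baseline, and the planned causal-forest double machine learning adjusts for covariates. If the residual SD falls by √(1 − ρ²), 80% power at 0.45 SD is reached at ρ of about 0.70 for 60 v 30, 0.79 for 30 v 30, and 0.85 between regimes with different first treatments at N = 60. The protocol gives no ρ, so adjustment neither rescues nor refutes the 0.80.

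Fourth, precision and power can legitimately meet in one calculation, through assurance on the half-width. Such a calculation exists, but it gives about 64 here.

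Fifth, the primary outcome is a derived strategy and not a hypothesis test, and no decision rule rests on 80% power. This limits the consequence but does not make the statement correct. It also argues against reading "A SMART design can determine whether treatment sequences matter" as a claim about this trial's power: that sentence is general rationale for the design type and needs no change. Likewise, the calculation is openly confined to the intervention group, so leaving out the control arm is a stated scope and not an error.

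**Conclusion.** The point holds in this form: 54 is a precision-based number, and the 0.80 beside it is attached to nothing. No reading tried that is consistent with 54 in both intervention arms together and about 30 per arm gives 80% power. On the stated assumptions, the unadjusted power for a 0.45 SD difference runs from about 29% to 51% across the whole-group comparisons, and is about 11% if 0.45 SD is the effect among one arm's non-responders. With the planned enrolment, the whole-group differences detectable at 80% power run from about 0.63 to 0.86 SD.

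The conclusion that power does not enter the reproduced figure depends on the SD-unit reading, which the exact match supports but the protocol does not state. The missing comparison and effect size are visible in the text and need no assumption.

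**What to change.** Rewrite the sentence in Sample Size and Power Analysis in three parts.

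1. Present 54 as precision-based, with estimand and unit. If the sponsor confirms the SD reading: 54 participants across the two intervention arms give a 95% confidence interval of half-width about 0.45 SD for the mean of one embedded regime, at a 0.60 response rate.
2. Delete the 0.80 power, or tie it to a named comparison and the difference the design can detect.
3. Add the differences detectable at 80% power for about 60 intervention and 30 control participants, labelled as unadjusted and in SD units: about 0.86 between regimes with different first treatments, 0.65 between regimes sharing one, 0.74 between first-stage arms, 0.63 versus control and, among non-responders only, 1.8 for switch versus double within one arm. Note that baseline adjustment would reduce these, by an amount that depends on a correlation the protocol does not give.

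The cost is a few lines of protocol text and a less favourable stated figure. No extra enrolment and no change to conduct is needed.
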